
**Table 1 tab1:** Schools’ inclusion and exclusion criteria.

Inclusion criteria	Exclusion criteria
The school has a specific space for parking bicycles and allows their parking	The school does not have specific infrastructure to park or store bicycles
The school has at least two classes per grade	The school offers bus transportation to the adolescents
At least eight students from the school will agree to participate in the study	The school is already participating in other interventions focused on promoting healthy behaviors
Schools from urban areas	The school has implemented an intervention to encourage commuting to school within the last year
	Schools from rural areas

**Table 2 tab2:** Participants’ inclusion and exclusion criteria.

Inclusion criteria	Exclusion criteria
Adolescents’ females and males aged from 12 to 17 years old (both ages included)	Adolescents younger than 12 years or older than 17 years
Healthy participants who can ride a bicycle safely and without difficulty.	Participants with any injury or medical condition that prevents safe participation in cycling to and from school
Be able to cycle to and from school at least 3 days per week during eight consecutive weeks (Intervention group)	Insufficient ability to ride a bicycle or inability to cycle to and from school at least 3 days a week (Intervention group)
Not to cycle to and from school more than 3 days a week during the last year	Participants who have cycled to and from school more than 3 days a week during the past year
To present a valid signed consent from their parents or legal guardians	Participants without a valid, signed parental or guardian consent form
To present valid data at baseline and follow-up from all the outcomes assessed	Participants who do not provide valid data for all assessed outcomes at baseline and follow-up

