#### Study assessment protocol

2.6.1

In Phase I, participants will perform three different simulations (i.e., commute by motorized-vehicle, walking, and cycling [see Figure 2]): (1) a simulation of driving to school will be performed by motorized-vehicle. After all the calibration process of the Cosmed K5 (both, flow and gas analyzers will be calibrated before every gas exchange measurement), a face-mask attached to the K5 will be place and gas exchange will be check during a two-minute period before the measurement start. After the check phase, gas exchange recording start during a five-minute period, while participants remain seated. Then, the participants will simulate commute in a motorized-vehicle by remaining seated in a chair for another 15-minute period, having previously walked for 2 mins simulating that participants are moving toward the motorized-vehicle from home. After this first simulation, there will be a five-minute period of cooling down. The total time of this first test will be 27 min. (2) A simulation walking to school will be conducted in a closed circuit defined by the research staff. The same procedures mentioned before will be followed. Then, the participant will walk for 15 min (the participant will determine the speed and intensity of walking) and finish with a five-minute cool down; (3) Participants will simulate a cycling route. They will wait for five-minute after walking and they will start cycling during 15-minute period along the designated route. The simulation will finish with a five-minute cool down period. The total time used in the walking and cycling simulations will be 45 min. These times were chosen because an average walking speed of 4.4–4.6 km/h would not exceed the distance Spanish adolescents are willing to walk to their educational center (1,350 m) (52). While no study in Spanish adolescents indicates the distance, they are willing to cycle to school, we estimated a distance of 4,200 m, the threshold distance used for Australian adolescents (53), with which a speed of approximately 15 km/h would not exceed 15 min. Detailed visual information on the evaluation and calibration process of the Cosmed K5 (Cosmed, Rome, Italy) can be found at the following link.^1^ In order that one active mode of commuting (e.g., walking) does not affect the post exercise oxygen consumption, thus PAEE, of the subsequent active mode of commuting (e.g., cycling), participants will alternate randomly by first performing the simulation of walking or cycling. In addition, the alternation of starting on the bike and walking will be counterbalanced by having the same number of participants starting on the bike or walking. Finally, all data will be downloaded using PC OMNIA.9 software v3.30.79 (Cosmed, Rome, Italy).

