##### Mode of active commuting to school and related outcomes

2.7.2.14

ACS will be evaluated using the PACO questionnaire^3^, a reliable and valid tool for young Spaniards (Kappa ranged from 0.42 to 0.94) (86, 87). The PACO questionnaire consists of four self-report items designed to assess the usual mode of commuting and the weekly frequency of commuting among children and adolescents. The four questions include: (i) *“How do you usually get to school?”* (ii) *“How do you usually get home from school?”* (iii) *“How did you get to school each day?”* and (iv) *“How did you get home from school each day?”* Participants will select their mode of commuting from predefined options such as walking, cycling, car, motorcycle, bus, public bus, metro/train/tram, or other (requiring mode specification). The main variables of interest are the percentage of usual cycling and active modes of commuting to and from school, along with the weekly number of cycling and active trips. Additionally, participants will report their distance from school and the time it takes to commute from home to school. Response options for distance range from less than 0.5 km to 5 km or more, while response options for travel time range from less than 15 min to 60 min or more (86). Other factors associated with ACS, such as independent mobility, will also be analyzed as secondary variables. Data will be aggregated by participant and collected during baseline and follow-up assessments. Overall, these questionnaires provide valuable data on modes of commuting, frequency of active commuting, distance covered, and time spent during the commute for both adolescents.

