##### Home-school distance

2.7.2.17

Distance from home to school will be determined using two objective methods. The first method calculates the shortest walking path between the participant’s home and school using Google Maps™ software (52). The second method combines GPS and Geographical Information System (GIS) data to establish the actual route taken by participants between home and school. Additionally, participants and parents will self-report their postal addresses, and the school’s postal address will also be obtained. These addresses will serve as reference points for both methods. The resulting variables will include the calculated shortest distance (km) and the actual route distance (km). Data will be aggregated by participant and collected during baseline and follow-up assessments.

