#### Analysis populations

2.10.1

In the ENERGYCO project, per-protocol and intention-to-treat (ITT) approaches, as well as sensitivity analyses, will be conducted. On one hand, the per-protocol approach will be used to present the main and secondary analysis. Participants from the intervention group who have cycled to and/or from school at least 3 days/week over 8 weeks will be included. Additionally, participants from both the intervention and control groups must have valid data at baseline and follow-up for the outcomes of interest (e.g., RMR and PAEE). On the other hand, the ITT approach will be used to present main and secondary analysis, but in the Supplementary material. This approach will include all participants in both the intervention and control groups who have valid data at baseline and follow-up or who have missing data at either baseline or follow-up. Finally, the potential impact of missing data will be assessed using various imputation models and sensitivity analyses. Specifically, we will conduct sensitivity analyses to determine whether the choice of imputation method affects the results. Additionally, no interim analyses will be performed.

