#### Statistical analysis

2.10.2

Descriptive analyses of all study variables presented with the mean (standard deviation) and frequencies (percentage) will be performed. Subsequently, the normality of the variables will be analyzed using histograms and normality tests. In Phase I, for the comparison of PAEE between the different modes of commuting (i.e., walking, cycling, and motorized-vehicle), a repeated measures ANOVA will be performed using the per-protocol approach. In addition, Student t-test or Mann–Whitney tests will be performed to compare the fluctuation of PAEE according to speed or distance commuted between active modes of commuting (i.e., walking vs. cycling).Within Phase II, the effects of the school-based cycling intervention on RMR and other health-related outcomes will be studied using an analysis of covariance (ANCOVA). Post-intervention RMR and other-health related values will be included as dependent variables, group (i.e., experimental group vs. control group) as fixed factor, and baseline outcome data as covariates. To evaluate the effect of the intervention on the secondary outcomes (i.e., physiological, physical, and psychosocial outcomes), we will conduct the same analysis used for the main outcomes (i.e., ANCOVA analysis using the intention-to-treat approach). Moreover, to control the variability between schools, the analyses will include adjustments for contextual and organizational variables, such as the SES of the school area, the length of cycling lanes, the availability of bicycle parking, and the level of engagement of teachers and students in the intervention. The estimates will be present as raw and standardized (z-scores; i.e., mean differences between follow-up and baseline data divided by the standard deviation), as an indication of the change the post-intervention z-scores will be calculated relative to the baseline mean and standard deviation. Effect sizes will be categorized as small (0.2 SDs), medium (0.5 SDs), and large (0.8 SDs), based on Cohen (93). Finally, to analyze the influence of covariates on the association between the intervention and the main outcomes (i.e., RMR and PAEE), mediation analyses will be performed. The intervention will be included as the independent variable, and the main outcomes as the dependent variables. Covariates included in the mediation analysis will encompass body composition, physical function, cognitive determinants, perceived barriers or autonomy, built-environment characteristics, weather, among others. In the statistical analysis, a value of *p* < 0.05 will be considered statistically significant.

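### Phase II fixes cycling exposure in days per week only, and the listed ANCOVA adjustments omit baseline home-school distance, on which the compared arms can differ systematically

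*Protocol article*

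**What the plan says.** **Exposure.** Table 2 lists among the inclusion criteria "Be able to cycle to and from school at least 3 days per week during eight consecutive weeks (Intervention group". Section 2.8 sets the same three-day target for adherence. For the per-protocol set, section 2.10.1 states: "Participants from the intervention group who have cycled to and/or from school at least 3 days/week over 8 weeks will be included". None of these gives a distance, a number of minutes or an amount of energy.

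**Distance.** Section 2.7.2.17 measures home-school distance in two ways, by the shortest path on Google Maps and by the route recorded with GPS: "The resulting variables will include the calculated shortest distance (km) and the actual route distance (km". Both are collected at baseline and follow-up.

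**Recruitment and allocation.** Section 2.4.1 gives distance as one reason why some pupils will be unable to join the cycling intervention. It places the draw of schools after the baseline assessment.

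**Analysis.** The Phase II ANCOVA in section 2.10.2 has "group (i.e., experimental group vs. control group) as fixed factor, and baseline outcome data as covariates". It adds school-level adjustments: area socioeconomic status, cycling-lane length, bicycle parking and engagement. Individual home-school distance is not named there, nor in the list for the mediation analysis. Section 2.10.1 presents main and secondary results per protocol, with intention-to-treat results in the supplement. A parenthesis in section 2.10.2 instead ties the ANCOVA to intention to treat.

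**The concern.** The Introduction says that intensity, duration and frequency together determine PAEE. Phase II fixes frequency alone, and duration follows largely from distance. Two things are at stake.

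The first is comparability. The ability criterion is marked for the intervention group. Because schools are drawn after baseline, a criterion for one arm can only act once the arm is known. The per-protocol cycling filter also acts on that arm only. If distance affects who can or does cycle, both steps select on distance in one arm and not in the other. Distance plausibly also bears on the outcomes, because a control pupil's usual travel depends on it. Schools with different catchments are the randomised unit, so chance imbalance is possible as well.

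The second is interpretation. The arm effect averages pupils with little added riding and pupils with a good deal, and no planned analysis separates them. Section 2.7.1.2 summarises Phase II PAEE as a mean rate in ml/min per trip, which does not carry trip duration.

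**Working it through.** **Inputs**
- Speed: about 15 km/h (section 2.6.1, Phase I planning).
- Trips: 3 days × 2 = 6 per week (Table 2, both directions).
- 4.2 km: "we estimated a distance of 4,200 m, the threshold distance used for Australian adolescents" (section 2.6.1), a Phase I design distance.
- 1.35 km: the distance that section 2.6.1 says Spanish adolescents are willing to walk.
- 0.5 and 5 km: the ends of a questionnaire scale in section 2.7.2.14, "Response options for distance range from less than 0.5 km to 5 km or more".

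None of these distances is an eligibility limit, and the documents give no distribution of distances. The ends are therefore assumptions.

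**The plan's own figure.** Section 2.6.1 says of 4.2 km that "a speed of approximately 15 km/h would not exceed 15 min". Minutes per trip = km / 15 × 60, so 4.2 km takes 16.8 min, and 15 min covers 3.75 km. The statement fails on its own figures. This does not affect the point here, but the passage needs reconciling.

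**Riding time**

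Minutes per week = 6 × km / 15 × 60 = 24 × km. Hours over 8 weeks = 8 × minutes per week / 60.

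| Distance (km) | Min per trip | Min per week | Hours in 8 weeks |
|---|---|---|---|
| 0.5 | 2.0 | 12 | 1.6 |
| 1.35 | 5.4 | 32.4 | 4.3 |
| 4.2 | 16.8 | 100.8 | 13.4 |
| 5 | 20.0 | 120 | 16.0 |

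Ratios: 4.2 / 1.35 = 3.1 and 5 / 0.5 = 10.

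The per-protocol wording accepts cycling in one direction, while Table 2 requires both. This widens the spread. Three one-way trips at 0.5 km give 6 min per week, and five days both ways at 4.2 km give 168, a ratio of 28.

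**What the covariate and the interaction can do**

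The planned effect is f = 0.25, which is d = 2f = 0.5 for two equal arms. With N = 250, the noncentrality is N f² = 250 × 0.0625 = 15.6, and the one-degree-of-freedom arm test has power 0.976, ignoring clustering.

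A simulation took N = 250, no clustering, distances uniform on 0.5 to 4.2 km in both arms, and an effect proportional to distance with mean d = 0.5. It gave these powers:
- arm effect without distance: 0.976
- arm effect with distance as a covariate: 0.977
- arm-by-distance term: 0.43

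The simulation gives both arms the same distance distribution, so it does not bear on selective imbalance. The bias from imbalance would be roughly the outcome slope on distance times the difference in mean distance between arms. The documents give neither quantity, so its size and direction cannot be stated.

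**The case against.** The case on the other side is that leaving out a baseline covariate does not bias a randomised comparison, that the power of the arm test hardly changes, and that the aim is the average effect over real commutes. The school-level adjustments and the mediation covariates are given as open lists. An optional effect-modification analysis could be left to an analysis plan. Distance is also not a clean measure of dose: pupils living near may already walk, so cycling may replace walking.

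Much of this stands. There is no case for the covariate on grounds of power, and an arm-by-distance term mixes minutes ridden with the travel mode displaced. Distance itself is not randomised.

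The first argument protects only a comparison of all randomised pupils. It does not cover a per-protocol comparison filtered in one arm. The mediation list does not fill the gap either, because baseline distance cannot be changed by allocation and so is not a mediator.

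A reader might infer that a null result could not be told from a small exposure. The documents do not support that. GPS records the distance, speed and duration of commutes for seven days at baseline and follow-up, heart rate is recorded on every cycling trip for eight weeks, and the PAEE equations use distance and speed. Delivered exposure can therefore be described afterwards. What is true is that no planned analysis distinguishes the two.

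**Conclusion.** The point holds in a limited form. Exposure is set in days per week only. At 15 km/h and six trips a week, riding time varies about 3-fold between 1.35 and 4.2 km and 10-fold between 0.5 and 5 km. These are contrasts between assumed ends and do not estimate the spread in this sample. A reader might settle on a single figure of about eight-fold by setting 0.5 km against 4.2 km (4.2 / 0.5 = 8.4). That pairs the bound of a questionnaire category with a Phase I design distance and should not be taken as a finding about the pupils.

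Baseline distance is collected but is not a named adjustment, although the criteria filter one arm on something related to it. The concern is strongest for the per-protocol analysis. It is weaker for an intention-to-treat analysis that keeps every randomised pupil, where only chance imbalance between schools remains. Whether distance predicts the outcomes, given their baseline values, is an assumption. The change is worth making because it is nearly free.

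**What to change.** In section 2.10.2:

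1. Add baseline shortest-path home-school distance (Google Maps) as a covariate in the Phase II models. Do not use the GPS route, which allocation can change.
2. Pre-specify, as a secondary and exploratory analysis in all randomised pupils, an arm-by-distance term with distance continuous, for RMR, PAEE and MVPA. Report effect estimates with confidence intervals at stated distances, not only a test. For PAEE, say that distance is an input to the predictive equation, so part of any gradient may arise by construction.
3. Reconcile the both-directions wording in Table 2 with the one-or-both wording in section 2.10.1, and the reference to intention to treat in section 2.10.2 with section 2.10.1.

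The cost is one covariate and one interaction term on data already collected, with no change to eligibility or to the intervention. The interaction will be imprecise and cannot separate minutes ridden from the mode displaced. The covariate reduces selection in the per-protocol set but does not remove it.

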#### School recruitment and randomization

2.4.1

In Phase I, a convenience sample of approximately 50 students will be recruited. A call to action will be used to engage adolescents through the development of infographics and information about the aims of this phase, which will be disseminated through social media, personal contacts, or emails. Since these tests will be conducted outside the school timetable, no schools will be directly contacted. Instead, parents or legal guardians will be responsible for contacting the research team if their children are interested in participating in the study and they provide their consent. In this call to action, incentives, such as activity wristbands will be given away to participating adolescents. For Phase II, a specific selection protocol will be implemented through a random draw. A list of all public secondary schools in each of the participating cities of the government educational institutions in Andalucía will be obtained. The schools in the three cities (Granada, Almería, Jaén) will be contacted by phone, and if they are interested in participating, they will have to meet a series of inclusion and exclusion criteria presented in Table 1. During the call, a meeting will be arranged with interested schools to explain to the management team and teaching staff the main objective of the study, as well as to obtain official consent to participate in the project from the school. After that, the research staff with the help of Physical Education teachers will recruit participants and their families, by visiting selected classes and explaining the study to prospective adolescent participants and finally requesting the family’s consent. The inclusion and exclusion criteria for the participants are presented in Table 2. To complete the sample of students in the intervention group, several schools may be needed, as not all students will be able to participate in the school-based cycling intervention due to family reasons, distance, predisposition, etc. To encourage as many students as possible from the intervention school to participate (with their families’ consent) in the school-based cycling intervention, an incentive system will be planned similar to other studies (42, 43). This incentive will consist of a voucher to be redeemed for sports equipment, provided that the participant has completed the 8 weeks of intervention and presents valid data at both baseline and follow-up. Once finished the baseline assessment, the participating schools will be randomly assigned through a draw to either a control or experimental group.

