### Description and rationale of the ENERGYCO study

2.5

In Phase I the PAEE of different modes of commuting will be quantified by analyzing each participant individually in different controlled environments. For phase II, after recruiting schools and participants, an eight-week school-based cycling intervention will be implemented. The choice of an eight-week duration was based on the results reported in the systematic review by Dorothea et al. (47) on the effects of cycling interventions in a school setting. For example, although interventions lasting longer than 8 weeks demonstrate positive changes in physical fitness (43, 48), they also exhibit lower adherence, with a higher dropout rate among participants post-intervention. Therefore, considering that interventions lasting 4 to 8 weeks show effects on self-efficacy (49) or PA levels (50) and report a lower dropout rate, an eight-week duration was chosen for the school-based cycling intervention. The intervention will consist of adolescents having to cycle to and school for eight consecutive weeks. To encourage participants to complete the intervention, they will take part in a *Bikeability* training and different encouragement strategies will also be used during this period. Moreover, the ENERGYCO school-based cycling intervention shows relevant factors described in the current National Education Law for the curriculum of Compulsory Secondary Education. This approach is based on strategies proposed by the Active Living by Design Community Action Model (51), which involves preparing through the development of interventions, promoting education, and motivating students to cycle anywhere, as well as organizing activities with incentives and programs to engage participants. Regarding the control groups, participants in these schools will be asked to continue their daily habits. In addition, at the end of the eight-week cycling intervention in schools, control schools will be given the opportunity to conduct the *Bikeability* sessions and will receive all the motivational strategies used for the participating adolescents.

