The second part of the intervention will consist of an eight-week program cycling to and from school. The duration of 8 weeks for school cycling is appropriate in this setting according to a previous systematic review (47). During the eight-week intervention, adolescents will receive an encouragement strategy every week in the form of a challenge related to knowledge content about the importance of PA and having good physical condition for our health, benefits of ACS, knowledge of RMR, PAEE, and its importance, promotion of confidence and motivation for adolescents to travel safely in their environment. The functioning of these encouragement strategies, called Octopus Strategy, will consist of eight games that will be opened weekly as the intervention progresses. In each of the games a series of points will be obtained, and these will be accumulated so that there will be a competition between the different participating schools. The winner of the Octopus strategy will be the participant who completes all the games during the 8 weeks. It is important to highlight that although motivational strategies will be employed to support adherence to the intervention, they are not intended to address broader behavior change processes, such as altering participants’ attitudes or intentions toward active commuting. Thus, the Octopus strategy will aim to improve the adherence and motivation to the intervention (i.e., to cycle at least 3 days to and from the school). Table 4 shows a summary of the project’s objectives related to the *Bikeability* sessions and the contents to be developed in the encouragement strategies, during the eight-week intervention. More information about the different challenges proposed by our research group as an encouragement strategy in the Supplementary material and in the following link.^5^

**Table 4 tab4:** Eight-week school-based cycling intervention overview: octopus strategy.

Activity		Aim	Content	Instrument (target)
1 (week 1 and 2)	Training 1:Bikeability	2, 4 & 5	Implementation of the basic guidelines for bicycle maintenance, in addition to the rules for entry, exit and parking of the bicycle Knowledge and practice of cycling skills on a circuit closed to traffic Practice driving skills on closed circuits to traffic	Bicycles, helmets, first aid kits, cones, and whistle. Student skills evaluation sheet (adolescents/teachers)

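### The eligibility ceiling (more than 3 days a week excluded) meets the adherence target (at least 3 days), so pupils already cycling exactly 3 days can enter either arm; a low-severity wording fix

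*Protocol article*

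**What the plan says.** Table 2 (section 2.4.1) sets the ceiling on earlier cycling twice, with the same threshold. The inclusion column reads "Not to cycle to and from school more than 3 days a week during the last year" and the exclusion column reads "Participants who have cycled to and from school more than 3 days a week during the past year". Both admit a pupil at exactly 3 days.

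Three other rules use the same number as a floor. Table 2 requires intervention pupils to be able to cycle at least 3 days a week. Section 2.8 gives the adherence goal as "to cycle at least 3 days to and from the school". Section 2.10.1 defines the per-protocol set, used for the main presentation of results, by the rule "Participants from the intervention group who have cycled to and/or from school at least 3 days/week over 8 weeks will be included".

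For controls, section 2.5 says that "participants in these schools will be asked to continue their daily habits". On timing, section 2.4.1 says: "Once finished the baseline assessment, the participating schools will be randomly assigned through a draw to either a control or experimental group". The ceiling is therefore applied before allocation and is the same in both arms.

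**The concern.** The ceiling and the floor meet at 3 days a week, and a pupil at that value satisfies both. In the intervention arm this pupil can pass the per-protocol filter without any change in behaviour. In the control arm the same pupil, following the instruction to keep usual habits, rides as often as the target asks.

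The trial estimates the effect of taking up cycling to school on resting metabolic rate (RMR) and physical activity energy expenditure (PAEE). Pupils whose cycling does not differ between arms contribute little to that contrast and pull the estimate towards zero. At any q above zero, 'adherent' would also no longer imply that behaviour changed.

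**Working it through.** **1. The thresholds side by side.** Let x be days a week of cycling to and from school in the past year.
- Eligible: x ≤ 3 (both columns of Table 2).
- At target: x ≥ 3 (sections 2.8 and 2.10.1).
- Overlap: x = 3. No other section closes it, and no rule caps cycling among controls.

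The rules also count trips differently: Table 2 refers to cycling to and from school, while section 2.10.1 accepts either direction. That could widen the overlap, but it is not used in the figures below.

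**2. Size of the dilution.** Let δ be the effect of moving to the target, and q the share already there, equal in both arms. Assume that these pupils gain nothing from the intervention.
- Comparing arms at follow-up: the intervention arm carries δ and the control arm qδ. The difference is δ − qδ = (1 − q)δ.
- Comparing change from baseline: the intervention arm changes by (1 − q)δ and the control arm by 0. The difference is again (1 − q)δ.

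These are two views of one loss and must not be added together.

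**3. The plan's own sample size (section 2.4.2).** Inputs: alpha 0.05, power 95%, effect size 0.25 (read as Cohen's f, hence d = 0.5 for two equal groups), two groups, ANCOVA F test with λ = N·f². With numerator df 1 this gives N = 210, not the stated 250; numerator df 2 gives 251. That mismatch is a separate matter. Here it means only that 250 analysed pupils and two groups give 97.6% power before any dilution.

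**4. Power with dilution.** N = 250, one covariate, clustering ignored, f = 0.25(1 − q):

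| q (assumed) | f | λ = 250·f² | d | Power at N = 250 | N for 95% |
|---|---|---|---|---|---|
| 0 | 0.2500 | 15.63 | 0.500 | 97.6% | 210 |
| 2% | 0.2450 | 15.01 | 0.490 | 97.1% | 219 |
| 5% | 0.2375 | 14.10 | 0.475 | 96.3% | 233 |
| 10% | 0.2250 | 12.66 | 0.450 | 94.3% | 259 |

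**5. Where 95% is lost.** The required N scales as 210/(1 − q)². It exceeds 250 when (1 − q)² < 210/250 = 0.84, that is 1 − q < 0.917, or q above about 8%.

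**The case against.** The strongest reply is that q is unknown and probably small. Section 2.4.2 cites the low prevalence of cycling to school in Spain, and the limitations in the Discussion repeat it as a threat to recruitment. Section 2.8 expects many participants to be out of practice and not regular riders. The overlap is a single value over a one-year look-back. For power to fall below 95%, roughly one participant in twelve would have to sit at that value. All of this stands. It is tempered only because the sample is not a general one: schools need bicycle parking, pupils must ride safely, and intervention pupils must be able to cycle at least 3 days a week. Pupils who already cycle may also pass the per-protocol filter more easily than novices. The article gives no figure that settles q.

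It is also fair to say that (1 − q) is a worst case for a given q. The target is a minimum, and a 3-day pupil in the intervention arm may ride more often. Baseline cycling is already recorded, so these pupils can be identified.

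A reader might infer that a 3-day control receives the whole intervention. The text does not support that, because the programme also includes two Bikeability sessions and weekly encouragement challenges. A reader might also infer that the two arms contribute separate, additive losses; step 2 shows that they do not.

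Baseline-adjusted ANCOVA (section 2.10.2) does not remove the point. It adjusts for the starting level of the outcome but cannot create a difference in exposure among pupils whose cycling is the same in either arm.

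**Conclusion.** The overlap is real, and nothing in the article resolves it. Its effect is attenuation of the contrast by at most (1 − q); it does not create a spurious benefit. Over an assumed range of q from 0 to 10%, power at 250 analysed goes from 97.6% to 94.3%, and it stays above the stated 95% until about 8%. These figures assume f = 0.25, two groups, no clustering, equal shares in both arms and no gain from the intervention among pupils already at 3 days.

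A reader might conclude that the planned power is lost. The documents do not support that: q is not stated, and what they say about prevalence points to the low end of the range. Severity is low. The point is worth making because the correction is nearly free and restores a clear meaning to adherence.

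**What to change.** In both rows of Table 2, replace 'more than 3 days a week' with '3 or more days a week', so that nobody already at the adherence target is eligible. In the same edit, make Table 2 and section 2.10.1 count one-way and return trips in the same way.

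If recruitment has started, leave the enrolled sample as it is and pre-specify a sensitivity analysis that excludes, from both arms, pupils at or above 3 days a week on the baseline PACO questionnaire (section 2.7.2.14). Because baseline precedes the draw of schools, this exclusion does not depend on allocation. PACO describes current commuting rather than the past year, so it approximates the eligibility rule.

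The cost is a wording change and a few lost candidates, or one additional analysis on data already being collected. With the overlap closed, the planned f = 0.25 is no longer diluted by this route, and power at 250 analysed is 97.6% under the same assumptions.
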